### Secondary Study Endpoints

*1. ***Antenatal medical and obstetric complications**including: pre-eclampsia or eclampsia *(systolic blood pressure ≥ 140 mmHg and diastolic ≥ 90 mmHg on two occasions four hours apart or more, and one of proteinuria (≥ 300 mg/24 hours or spot urine creatinine ratio ≥ 30 mg/mmol), renal insufficiency (serum plasma creatinine ≥ 0.09 mmol/L or oliguria), liver disease (elevated serum transaminases &/or right upper quadrant pain), neurological disturbances (convulsions, hyperreflexia with clonus, severe headache with hyperreflexia, persistent visual disturbances), or haematological disturbances (thrombocytopaenia, disseminated intravascular coagulopathy, haemolysis),)*[16] antepartum haemorrhage requiring hospitalisation; and abnormal umbilical artery Doppler study *(absent or reversed end diastolic flow as detected by ultrasound examination).*

2. **Labour and birth complications**including: induction of labour for medical or obstetric complications; meconium stained liquor; cardiotocogram (CTG) abnormality during labour (*fetal tachycardia (fetal heart rate greater than 160 bpm); fetal bradycardia (fetal heart rate less than 110 bpm); reduced variability (less than 5 bpm); decelerations of the fetal heart rate (early, late or variable))*; instrumental vaginal birth; emergency caesarean birth (*all and for fetal distress).*

3. **Adverse outcomes for the infant**defined as: Apgar score <7 at 5 minutes; birthweight less than 10^th ^centile for gestational age and infant sex; admission to neonatal intensive care unit (NICU) and length of stay; incidence and severity of any neonatal respiratory disease; use of and length of any mechanical ventilation; use of and length of any tube feeding.

4. **Composite of serious neonatal outcomes reflecting asphyxia**defined as one or more of: *death due to asphyxial causes*; *birth trauma *(subdural or intra-cerebral haemorrhage, spinal cord injury, basal skull fracture, other fracture, peripheral nerve injury present at discharge from hospital); *birth weight ≤ 3*^*rd *^*centile for gestational age at birth and infant sex *[8]; *Apgar score ≤ 4 at 5 minutes of age; cord pH ≤ 7.00 *[9]; *seizures at ≤ 24 hours age or requiring two or more drugs to control; neonatal encephalopathy grade 3 or 4 *[14]).

5. **Composite of serious neonatal outcomes reflecting immaturity**defined as one or more of: *death due to immaturity causes; use of ventilation ≥ 24 hours; admission to neonatal intensive care unit (NICU) ≥ 4 days; severe respiratory distress syndrome *(MAP ≥ 10 and or FiO_2 _≥ 0.8 with need for ventilation)*; neonatal encephalopathy grade 3 or 4 *[14]*; chronic lung disease defined as continued oxygen requirement at 28 days of life; proven necrotising enterocolitis; proven systemic infection within 48 hours of birth treated with antibiotics.*

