#### Trial hypotheses

**The primary hypothesis **of this randomised trial is that for women with a twin pregnancy elective timing of birth at 37 weeks gestation is associated with

• **a reduction in serious adverse outcome for the infant**, defined as one or more of stillbirth, neonatal death or significant infant morbidity.

**The secondary hypotheses **of the trial are that for women and infants of a twin pregnancy elective timing of birth at 37 weeks gestation compared with standard management is associated with

• a reduction in antenatal medical and obstetric complications

• a reduction in labour and birth complications

• a reduction in other infant complications

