## Analysis and Reporting of Results

We will conduct an interim analysis when we have recruited 50% of the total sample size (230 women).

The initial analysis will examine the baseline characteristics of all randomised women, as an indication of comparable treatment groups, and include maternal age, race, height, weight, smoking history, past obstetric history (including previous perinatal loss), and chorionicity of the pregnancy. Any important differences in these prognostic variables will be controlled for in subsequent analyses. Outcome comparisons for women and infants will be analysed for the primary and secondary outcomes on an "intention to treat" basis, according to treatment allocation at randomisation. Continuous outcomes will be analysed using linear mixed model regression. Binary outcomes will be analysed using a generalised linear mixed model with a log link function and binomial distribution. A random effect to account for clustering of babies from multiple births will be included. If models do not converge, then alternative methods of accounting for multiple births using robust variance estimation will be explored. Results will be presented as relative risks with 95% confidence intervals. The level of significance will be 0.05 and all p values will be two-sided.

Pre-specified subgroup analyses will be by chorionicity of the pregnancy (monochorionic or dichorionic); collaborating centre; and actual mode of birth.

Approval to conduct this study has been obtained from the following research and ethics committees: Women's and Children's Hospital (Adelaide, South Australia); Lyell McEwin Health Service (Adelaide, South Australia); The Royal Women's Hospital (Melbourne, Victoria); Sydney West Area Health Service (New South Wales); Northern Sydney Central Coast (New South Wales); Mater Health Services (Brisbane, Queensland); Redcliffe-Caboolture Health Service (Queensland); Logan Hospital (Queensland); Townsville Health Service (Queensland); Mackay Base Hospital (Queensland); and Auckland City Hospital (New Zealand).

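### The pre-eclampsia/eclampsia endpoint needs both systolic and diastolic pressure raised twice, so women with one raised pressure plus an organ feature, and some with diagnosed eclampsia, score as no event

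*Protocol article*

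**What the plan says.** Item 1 of Secondary Study Endpoints lists pre-eclampsia or eclampsia, under one joint definition, among the antenatal medical and obstetric complications. The definition has two parts, and both are required:

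- Pressure: "systolic blood pressure ≥ 140 mmHg and diastolic ≥ 90 mmHg on two occasions four hours apart or more".
- Organ involvement: "and one of proteinuria (≥ 300 mg/24 hours or spot urine creatinine ratio ≥ 30 mg/mmol", or renal, liver, neurological or haematological involvement.

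Convulsions appear only in the second part: "neurological disturbances (convulsions, hyperreflexia with clonus, severe headache with hyperreflexia, persistent visual disturbances". In the same sentence, the liver criterion is written so that either finding is enough: "liver disease (elevated serum transaminases &/or right upper quadrant pain".

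The definition appears once, with a citation to reference 16. No other section gives an exception for severe features or for eclampsia. The endpoint group serves the first secondary hypothesis in Trial hypotheses, "a reduction in antenatal medical and obstetric complications".

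**The concern.** The two pressures are joined by a plain conjunction, so the pressure part works as a gate. If only one of them is raised, however persistently, no organ feature can make the woman a case. A research assistant abstracting case notes to this text would have to record no event for her.

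Eclampsia is the clearest instance. It is in the endpoint's name but has no criterion of its own. A convulsion counts only as one of several organ features behind the same gate, so a diagnosed eclamptic convulsion can fail the definition of an endpoint named after it.

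What is at stake is a lower event count, and so a wider interval, for one maternal outcome. If some sites treated one raised pressure as sufficient and others did not, scoring would also be inconsistent between centres.

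**Working it through.** The document states no rate, power or sample size for this endpoint, so there is no figure to reproduce. The check is of the rule's logic.

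**1. The rule in symbols.** Let S = systolic ≥ 140 mmHg and D = diastolic ≥ 90 mmHg, each on two occasions at least four hours apart, and O = at least one listed organ feature.

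- As printed: event = (S and D) and O.
- Either-pressure rule: event = (S or D) and O.

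**2. Truth table** for women whose pressures persist on two such occasions and who have an organ feature (O true):

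| Pressure (mmHg) | As printed | Either pressure |
|---|---|---|
| 165/85 | no event | event |
| 135/95 | no event | event |
| 165/95 | event | event |
| 135/85 | no event | no event |

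The rules differ exactly where one pressure is raised and the other is not.

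**3. Can the printed conjunction be read as a loose alternative?** The text does not support that. The liver criterion in the same sentence marks its alternatives explicitly, and the severe respiratory distress criterion in Primary Study Endpoint does so too. The authors signal alternatives when they mean them.

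**4. Eclampsia.** A convulsion makes O true and leaves S and D unchanged. A diagnosed eclamptic convulsion with only one pressure raised, or with both raised on a single recorded occasion, gives (S and D) false and therefore no event.

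**5. What equal under-counting would do (illustration only).** Assumptions not in the document: true rates of 10% and 5%, and a fraction s of true cases captured equally in both arms. The article's 460 women split equally give 230 per arm. The test is two-sided at 0.05, as in Analysis and Reporting of Results ("The level of significance will be 0.05 and all p values will be two-sided").

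- Relative risk = 0.05s / 0.10s = 0.50 for every s, so it does not change.
- With p1 = 0.10s, p2 = 0.05s, n = 230 and m = (p1 + p2)/2, power = Φ{[(p1 − p2) − 1.96·√(2m(1 − m)/n)] / √([p1(1 − p1) + p2(1 − p2)]/n)}.
- For s = 1: [0.05 − 1.96 × 0.02456] / 0.02445 = 0.076, so power = 53%.

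| Captured (s) | 100% | 90% | 80% | 70% | 60% |
|---|---|---|---|---|---|
| Power | 53% | 49% | 44% | 39% | 34% |

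The table shows the kind of harm, which is lost precision with an unchanged ratio. It does not estimate s, because the document contains nothing from which s could be obtained.

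**The case against.** **A stricter definition may be deliberate.** Requiring both pressures could be a choice for specificity, and the definition is attributed to a source that is not at hand. It would be wrong to assert that the wording departs from that source, and this stands as a limit. It does not rescue the rule for eclampsia, where the conflict is between the definition and the endpoint's own name.

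**The second reading could come at any time.** The text does not require both readings to precede the convulsion or the birth, and outcomes are abstracted from notes afterwards. The antenatal heading leaves this open. So one cannot say that expedited birth necessarily removes cases. The gate on both pressures does not depend on timing, however.

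**Bias between arms.** A reader might infer that the four-hour requirement discards cases unequally, because the arms differ in when birth is planned. The document does not support this: one definition applies to both arms, and nothing in it shows that capture differs or in which direction.

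**The size of the loss.** A reader might want to put a percentage or a number of cases on it. The document gives neither the distribution of pressure patterns nor an expected rate of pre-eclampsia.

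**The urine test.** The criterion reads "spot urine creatinine ratio ≥ 30 mg/mmol" and omits the numerator. A reader might call it unusable, but it sits inside the definition of proteinuria and its unit points to a protein:creatinine ratio. A word has been dropped.

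**Importance.** This is one component of one of five secondary endpoint groups. It enters neither the primary composite nor the sample size, and the order of listing confers no rank. All of that stands and limits the weight of the point.

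**Conclusion.** The point holds as a defect in a stated rule. Followed as printed, the definition scores as no event any woman with persistent elevation of only one pressure and a listed organ feature, and any woman with diagnosed eclampsia who did not have both pressures raised twice. The second consequence contradicts the endpoint's name. This is not a detail left to a fuller document, since the article prints a complete operational definition with thresholds.

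The expected consequence is under-counting and lost precision on a single secondary component. If capture is equal in the two arms, the relative risk is unchanged in expectation. The conclusion rests on the printed wording alone and makes no claim about what reference 16 says.

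**What to change.** For outcome classification only, with no change to any woman's care:

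1. Check the printed definition against reference 16 and reconcile the two.
2. Write the pressure criterion as systolic ≥ 140 mmHg and/or diastolic ≥ 90 mmHg, keeping the organ criterion as an added condition.
3. State that diagnosed eclampsia counts as an event without the two-readings requirement.
4. As an editorial correction, insert protein before creatinine ratio.

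The cost is one changed line in the definition and on the data form. Case notes are already abstracted after birth (Follow up of Women in Both Groups), so no new data source should be needed, provided the pressures are recorded there. The downside is a slightly less specific case definition. The revised rule should be applied to all records in both arms, without reference to allocation.

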### Primary Study Endpoint

A composite mortality and morbidity index has been chosen as the primary outcome for the trial. For a policy of elective birth at 37 weeks gestation to be justified in clinical practice, there must be an important benefit of reduced perinatal mortality or serious adverse outcome for the infants defined as one or more of the following:

• **Perinatal mortality**defined as *any fetal death after trial entry, or death of a liveborn infant within 28 days of age (excluding lethal congenital anomalies); *or

• **Serious neonatal morbidity**defined as one or more of the following, excluding lethal congenital anomalies, and reflecting either **asphyxia **(*birth trauma *(subdural or intracerebral haemorrhage, spinal cord injury, basal skull fracture, other fracture, peripheral nerve injury present at discharge from hospital); *birth weight ≤ 3^rd ^centile for gestational age at birth and infant sex *[8]; *Apgar score ≤ 4 at 5 minutes of age; cord pH ≤ 7.00 *[9]; *seizures at ≤ 24 hours age or requiring two or more drugs to control; neonatal encephalopathy grade 3 or 4 *[14]) or **immaturity **(*use of ventilation ≥ 24 hours; admission to neonatal intensive care unit (NICU) ≥ 4 days; severe respiratory distress syndrome *(MAP ≥ 10 and or FiO_2 _≥ 0.8 with need for ventilation)*; neonatal encephalopathy grade 3 or 4 *[14]*chronic lung disease defined as continued oxygen requirement at 28 days of life; proven necrotising enterocolitis; proven systemic infection within 48 hours of birth treated with antibiotics).*

These definitions of adverse outcome are those used by the Australian and New Zealand Neonatal Network,[15] and those considered by experts as important measures of term and post-term neonatal morbidity [10].

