### Sample Size

The incidence of serious adverse infant outcome is the principal endpoint of the trial. Using a composite neonatal morbidity and mortality index based on perinatal mortality, admission to NICU for greater than or equal to four days, and birthweight less than the third centile for gestational age at birth and infant sex, the occurrence of serious adverse neonatal outcome for infants of a twin pregnancy born at 37 weeks gestation or more is estimated at 16.3% [4]. To reduce this to the rate of 6.7% seen in singleton infants at the same gestational age [4], and adjusting for the clustering of twin infants within mothers, a sample size of 460 women with a twin pregnancy at ≥ 37 weeks gestation will be required, using a p-value of 0.05 (two tailed) and power 80%.

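### Grade 3 or 4 neonatal encephalopathy is listed in both the asphyxia and the immaturity composite with no cause qualifier, so every affected infant counts in both secondary endpoints

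*Protocol article*

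**What the plan says.** The Primary Study Endpoint section of the protocol article introduces serious neonatal morbidity as "defined as one or more of the following, excluding lethal congenital anomalies, and reflecting either" asphyxia or immaturity, and then lists items under each heading. The Secondary Study Endpoints section turns each heading into an endpoint of its own: item 4, "Composite of serious neonatal outcomes reflecting asphyxia", and item 5, "Composite of serious neonatal outcomes reflecting immaturity".

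The entry "neonatal encephalopathy grade 3 or 4" stands in item 4 and again in item 5, with the same grade and the same reference number, and neither mention is limited to a cause. It also stands under both headings of the primary endpoint. Deaths are handled differently: item 4 takes "death due to asphyxial causes" and item 5 takes "death due to immaturity causes".

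**The concern.** The Background section on induction of labour describes a balance: fewer deaths and less morbidity from earlier birth, against risks of early birth such as respiratory distress and neonatal unit admission. The primary composite pools outcomes from both sides. The two secondary composites exist so that a reader can look at each side separately.

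An item that enters both composites whatever its cause works against that purpose. An infant whose encephalopathy is asphyxial is recorded as an immaturity event as well. An infant who dies of an asphyxial cause after grade 3 or 4 encephalopathy is kept out of the immaturity composite by the rule for deaths and brought back in by the encephalopathy item. If earlier birth lowers asphyxia and raises immaturity, the shared events make both estimated effects a little less distinct.

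**Working it through.** No figure in the article depends on this item, so the check is a comparison of the lists, followed by an illustration with assumed values.

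**Step 1: compare the lists** (Primary Study Endpoint; Secondary Study Endpoints, items 4 and 5).

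- Asphyxia only: birth trauma; birth weight at or below the 3rd centile; low 5-minute Apgar score; low cord pH; seizures. Five items.
- Immaturity only: ventilation of at least 24 hours; NICU stay of at least 4 days; severe respiratory distress syndrome; chronic lung disease; necrotising enterocolitis; early systemic infection. Six items.
- Both: grade 3 or 4 encephalopathy. One item.

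The pattern is the same in the primary and the secondary definitions, so it is not a fault of text extraction. No section gives a rule that assigns a case to one mechanism.

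**Step 2: effect on the primary composite.** The primary endpoint is met by one or more items, so an infant counts once. There are 5 + 6 + 1 = 12 distinct morbidity items. Removing one of the two mentions of encephalopathy leaves the same 12.

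**Step 3: number of infants.** The Sample Size section gives 460 women, hence 460 × 2 = 920 infants. The encephalopathy rate is not given; 1 to 5 per 1,000 is assumed.

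- 920 × 0.001 = 0.92
- 920 × 0.005 = 4.6

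These figures are an upper bound on the infants whose immaturity status would change. If an assumed 50% to 95% of affected infants also meet the NICU or ventilation item, the range becomes 0.92 × 0.05 = 0.05 to 4.6 × 0.50 = 2.3 infants, both arms together.

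**Step 4: shift in the immaturity relative risk.** Let p be the standard-care rate of the immaturity composite without the item. Let e be the standard-care rate of asphyxial encephalopathy that meets no other immaturity item. Assume relative risks (elective birth versus standard care) of 1.5 for immaturity and 0.5 for asphyxia. All four inputs are assumptions.

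Observed RR = (p × 1.5 + e × 0.5) / (p + e)

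- p = 10%, e = 0.1%: (0.150 + 0.0005) / 0.101 = 1.49
- p = 5%, e = 0.2%: (0.075 + 0.001) / 0.052 = 1.46
- p = 2%, e = 0.5%: (0.030 + 0.0025) / 0.025 = 1.30

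The last line combines the lowest assumed immaturity rate with the highest assumed encephalopathy rate and no overlap with other items. If half of those infants also meet another immaturity item, e falls to 0.25% and the result is (0.030 + 0.00125) / 0.0225 = 1.39.

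**The case against.** The strongest reply is that this one item does little. The NICU and ventilation items in the immaturity list carry no cause qualifier either. A sick asphyxiated or growth-restricted infant can enter the immaturity composite through them, and an infant with severe encephalopathy plausibly would. This stands: it makes the counts above an upper bound, and it means that some overlap remains whatever is done about encephalopathy. A reader might infer that this item alone makes the two composites inseparable. The lists do not support that, because the overlap exists without it.

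A reader might also infer that these composites are the only place where benefit and cost can be told apart, so that a null or mixed primary result could not be explained. The article does not support that. Item 3 of the secondary endpoints reports respiratory disease, NICU admission and stay, and mechanical ventilation individually, alongside a low Apgar score.

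A third reply is that nothing says the composites must divide events without overlap, and that the double listing may be deliberate. Each composite is indeed a valid binary endpoint by itself. But the either-or wording, the absence of any other shared morbidity item and the division of deaths by cause all point to an intended separation. That the item was copied by mistake is only an inference, since the sources cited for the definitions and the grading are not at hand.

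**Conclusion.** The point holds as a small error in two fixed endpoint definitions. By the text alone, every infant with grade 3 or 4 encephalopathy meets secondary endpoints 4 and 5 whatever the cause, which is inconsistent with how the same endpoints treat deaths.

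At the assumed 1 to 5 per 1,000, at most about 1 to 5 of 920 infants are involved, and probably fewer would change status. The pull on the two treatment effects is usually slight; it would be noticeable only if the immaturity composite had few events and encephalopathy were at the top of the assumed range. Its direction assumes that the two mechanisms respond differently to earlier birth.

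The primary composite as listed, the sample size and the type I error are unaffected. An analysis plan that followed these lists would carry the overlap forward, so the point is not one merely left to a later document.

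**What to change.** Settle the assignment before any results by arm are seen, including those of the interim analysis at 230 women, so that the choice cannot appear to depend on the outcome. Either of two changes is enough:

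- count grade 3 or 4 encephalopathy in the asphyxia composite only; or
- keep it in both lists but assign each case by cause, as is already done for deaths.

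If a different immaturity item was meant in that position, name it. That item would then also join the primary composite, so the primary definition should be checked in the same step. Align the Primary Study Endpoint section with items 4 and 5 of the Secondary Study Endpoints, and say in the report that the NICU and ventilation items leave some overlap between the composites.

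The first option costs wording and one line of derivation code, with no new data. The second needs slightly more work, because someone must judge the cause of each case, but few cases are expected.

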### Sample Size

The incidence of serious adverse infant outcome is the principal endpoint of the trial. Using a composite neonatal morbidity and mortality index based on perinatal mortality, admission to NICU for greater than or equal to four days, and birthweight less than the third centile for gestational age at birth and infant sex, the occurrence of serious adverse neonatal outcome for infants of a twin pregnancy born at 37 weeks gestation or more is estimated at 16.3% [4]. To reduce this to the rate of 6.7% seen in singleton infants at the same gestational age [4], and adjusting for the clustering of twin infants within mothers, a sample size of 460 women with a twin pregnancy at ≥ 37 weeks gestation will be required, using a p-value of 0.05 (two tailed) and power 80%.

